## Abstract

**Background:**

Diabetic kidney disease (DKD) remains one of the leading causes of premature death in diabetes. DKD is classified on albuminuria and reduced kidney function (estimated glomerular filtration rate (eGFR)) but these have modest value for predicting future renal status. There is an unmet need for biomarkers that can be used in clinical settings which also improve prediction of renal decline on top of routinely available data, particularly in the early stages. The iBEAt study of the BEAt-DKD project aims to determine whether renal imaging biomarkers (magnetic resonance imaging (MRI) and ultrasound (US)) provide insight into the pathogenesis and heterogeneity of DKD (primary aim) and whether they have potential as prognostic biomarkers in DKD (secondary aim).

**Methods:**

iBEAt is a prospective multi-centre observational cohort study recruiting 500 patients with type 2 diabetes (T2D) and eGFR ≥30 ml/min/1.73m^2^. At baseline, blood and urine will be collected, clinical examinations will be performed, and medical history will be obtained. These assessments will be repeated annually for 3 years. At baseline each participant will also undergo quantitative renal MRI and US with central processing of MRI images. Biological samples will be stored in a central laboratory for biomarker and validation studies, and data in a central data depository. Data analysis will explore the potential associations between imaging biomarkers and renal function, and whether the imaging biomarkers improve the prediction of DKD progression. Ancillary substudies will: (1) validate imaging biomarkers against renal histopathology; (2) validate MRI based renal blood flow measurements against H_2_O^15^ positron-emission tomography (PET); (3) validate methods for (semi-)automated processing of renal MRI; (4) examine longitudinal changes in imaging biomarkers; (5) examine whether glycocalyx and microvascular measures are associated with imaging biomarkers and eGFR decline; (6) explore whether the findings in T2D can be extrapolated to type 1 diabetes.

**Discussion:**

iBEAt is the largest DKD imaging study to date and will provide valuable insights into the progression and heterogeneity of DKD. The results may contribute to a more personalised approach to DKD management in patients with T2D.

**Trial registration:**

Clinicaltrials.gov (NCT03716401).

## Background

### The BEAt-DKD project

Diabetic kidney disease (DKD) is the leading cause of end stage renal disease [1, 2]. It is currently estimated that approximately 20–40% of people with diabetes will develop DKD [3], and this is expected to rise in the future. With the global increase in the prevalence of diabetes [4], particularly type 2 diabetes (T2D), DKD is reaching epidemic proportions, with health and quality of life implications (e.g. increased risk of cardiovascular mortality) for the individual [5]. Even with current approaches for the management of diabetes and renin-angiotensin-aldosterone system blockade, there is still a large residual risk in DKD [6].

DKD is routinely classified clinically based on albuminuria and reduced kidney function (estimated glomerular filtration rate (eGFR)). Albuminuria is traditionally viewed as a hallmark of diabetes related kidney damage. However, there are limitations of using albuminuria to classify DKD, which include the need for multiple measurements to mitigate spurious results due to factors such as infection and physical activity. Additionally, the heterogeneity of DKD is increasingly recognised, as reflected, for example, by the disparity in DKD progression (fast versus slow DKD progression) and by patients with declining kidney function but normoalbuminuria. For example, 51% of participants in the UK Prospective Diabetes Study whose eGFR declined below 60 ml/min/1.73 m^2^ had normoalbuminuria [7]. This heterogeneity in DKD highlights the need for novel biomarkers and a more personalised medicine-based approach to managing DKD.

The fundamental aim of the Biomarker Enterprise to Attack DKD (BEAt-DKD) consortium is to increase our understanding of the pathogenesis and heterogeneity of DKD, enabling the identification of novel biomarkers and treatment targets, to facilitate a more personalised medicine-based approach to managing DKD and increase the efficiency of clinical trials [8].

### Imaging biomarkers for DKD

Cross-sectional imaging, in particular MRI and US, is increasingly proposed as an alternative source of biomarkers to inform chronic kidney disease (CKD) management [9, 10]. An important example is the qualification by the Food and Drug Administration (FDA) and the European Medicines Agency (EMA) of Total Kidney Volume (TKV) as a prognostic enrichment biomarker for Autosomal Dominant Polycystic Kidney Disease (ADPKD) – one of only a handful of clinical biomarkers approved by the FDA so far [11, 12]. In recent years the interest is increasingly moving towards advanced MRI and US techniques that are sensitive to structural and functional tissue characteristics such as perfusion, oxygenation, blood flow, glomerular filtration, tubular flow, fibrosis, inflammation, metabolism and tissue composition. Additional utility derives from the fact that these characteristics can be measured separately for left and right kidney and for cortex and medulla, and that they can characterise functional and structural heterogeneity within those areas.

A number of preclinical and single-centre clinical studies have indicated a potential utility of MRI and US biomarkers in DKD specifically. For instance, US-based measurements of kidney volume have suggested that kidney enlargement is associated with poorer outcomes in early and advanced DKD, despite the often better GFR of larger kidneys [13–15]. A possible explanation is that hypertrophy indicates a sustained state of primary or secondary hyperfiltration and associated damage due to intraglomerular pressures. A mechanistic study suggested that the MRI method BOLD (Blood Oxygenation Level Dependent MRI) can highlight areas at risk of ischemic damage due to oxygen depletion after sustained hyperfiltration [16], and recent clinical studies have confirmed that the BOLD signal is predictive of CKD progression [17, 18]. Some biomarkers derived from diffusion-weighted MRI are sensitive to renal fibrosis [19, 20], can identify microstructural changes after sustained hyperfiltration [21], and can potentially detect disease progression earlier than eGFR [22]. Kidney perfusion can also be measured with MRI and has shown a correlation with eGFR in DKD [23]. Other non-renal imaging biomarkers characterising general risk factors for diabetes and its associated complications may be relevant in this context as well and can easily be measured in the same MRI scan session, such as liver and pancreatic fat fraction [24].

### iBEAt study aims and objectives

The aim of iBEAt is to evaluate the utility of imaging biomarkers in DKD in a large cohort of heterogeneous T2D patients, in the early stages of DKD where there is high potential for effective interventions to slow the rate of DKD progression.

The key hypotheses are that (1) imaging biomarkers of DKD provide additional information on the pathogenesis and histological and clinical heterogeneity of DKD compared to biomarkers sourced from blood or urine samples or physical exams, and that (2) changes in imaging biomarkers precede increases in albuminuria and decline in kidney function as measured by eGFR slope. As a result, we expect imaging biomarkers to improve the identification of DKD patients at risk of rapid decline in kidney function, either when used alone or combined with clinical data or biological fluid biomarkers.

An additional aim of the iBEAt study is to establish a biobank of biological samples (blood- and urine-based) from well-characterised patients not only for use within the BEAt-DKD programme but also for future DKD collaborative studies with scientists outside BEAt-DKD. This will facilitate biomarker discovery studies using novel blood- and urine-based biomarkers and may serve as the foundation for a comprehensive multi-scale phenotyping strategy linking data from blood, urine, tissue, microvascular assessments, imaging, physical measurements and medical histories.

The specific study objectives are:
Primary objective: To examine whether renal imaging biomarkers are associated with severity of DKD as defined using classical biomarkers of DKD, albuminuria and eGFR, in individuals with T2D and eGFR ≥ 30 ml/min/1.73m^2^.Secondary objective: To examine whether renal imaging biomarkers at baseline are associated with changes in renal function over time as measured by eGFR slope over a subsequent 3-year period.

### Overview of iBEAt study design and organisation

iBEAt is a prospective observational study that will enrol 500 participants with T2D and eGFR greater than 30 mL/min/1.73m^2^ across multiple European centres.

A schematic overview of the study assessments is presented in Table 1. At baseline, medical histories will be collected for each participant and they will undergo comprehensive renal imaging (MRI and US), biological sample collection (blood and urine) and physical measurements. They will then be invited back annually for 3 years, where all measurements except the imaging will be repeated.

**Table 1 Tab1:** Overview of the study showing type of data collected (rows) for each time point (columns)

*Protocol Details*	*Screening*	*Baseline*	*Year 1*	*Year 2*	*Year 3*
***Time Window***	***Day 0***	***0-3 m***	***1y ± 3 m***	***2y ± 3 m***	***3y ±*****3*****m***
*Informed Consent*	*X*				
*Demographics*	*X*				
*Clinical Information*		*X*	*X*	*X*	*X*
*Local lab value collection*	*X*	*X*	*X*	*X*	*X*
*Blood Collection (including DNA and RNA)*		*X*	*X*	*X*	*X*
*Urine Collection (random)*	*X*				
*Urine Collection (1st morning & additional void)*		*X*	*X*	*X*	*X*
*MRI*		*X*			
*US*		*X*			

*y* year, *m* month

The organisation of iBEAt is shown in Fig. 1. The study is led by the coordinating centre in Sheffield with a co-lead in Exeter and a study manager in Michigan. Currently there are 5 recruiting centres (University of Leeds, University of Exeter Medical School, University of Bari, University of Bordeaux and University of Turku), a central laboratory (Lund University) and a central data repository (Swiss Institute of Bioinformatics (SIB)). University of Sheffield is the central imaging processing and quality assurance (QA) site, with support from Antaros Medical (Sweden) for biomarkers of body composition. All ethical and relevant local approvals are in place at each recruiting site. As a BEAt-DKD work package the study is supported by the BEAt-DKD consortium Steering Committee and an external Scientific Advisory Board.

**Fig. 1 Fig1:**
[figure not shown]
Overview of study organisation. iBEAt study organigram showing central roles (grey ellipse) and recruiting sites with ancillary studies (circles). BMs = biomarkers; QA = quality assurance; RBF = renal blood flow; PET = Positron-emission tomography; SIB = Swiss Institute of Bioinformatics; T1D = type 1 diabetes; Umich = University of Michigan

## Methods

### iBEAt participants

The iBEAt study will recruit participants with a diagnosis of T2D, eGFR greater or equal to 30 mL/min/1.73m^2^, aged between 18 and 80 years, who are able to give informed consent, and do not satisfy any of the exclusion criteria. The exclusion criteria are listed in Table 2 (see also additional file 3.0).

**Table 2 Tab2:** List of iBEAt exclusion criteria (see also additional file 3.0)

*Permanent dialysis*	*Current metastatic malignancy*
*Renal transplantation*	*Current malignancy with expected survival < study follow up period (4 years)*
*Known clinical history of urinary obstruction on renal US*	*Melanomatous skin cancer < 5 years ago (fully resected melanoma > 5 years ago,* i.e. *surgical cure, can be recruited)*
*Post-voiding residue over 100 ml, or pyelectasis*	*Use of investigational drug within 1 month prior to screening*
*Known clinical history of aortic endoprothesis at the renal level*	*Current pregnancy*
*Known current or clinical history of renal or urinary tract malignancy*	*Use of antiretroviral medication*
*Biopsy proven non-diabetic primary renal disease*	*History of Hepatitis B or Hepatitis C*
*Autosomal dominant polycystic kidney disease (APKD)*	*Significant comorbidities with life expectancy of < 1 year*
*Cirrhotic liver disease or non-cirrhotic chronic liver disease where alanine aminotransferase > 2 x upper limit of normal*	*Standard contrast enhanced-MRI exclusions (*e.g. *cochlear implant, aneurysm clips, claustrophobia and known allergy to Gadolinium contrast)*
*Renal stones causing CKD*	*Any other significant disease or disorder which, in the opinion of the investigators, may either put the patient at risk because of participation in the study, or may influence the result of the study, or the patient’s ability to participate in the study*

iBEAt will recruit across the A1-A3 albuminuria range (normo-, micro- and macroalbuminuria) and the G1-G3 eGFR range (G1: ≥90; G2: 60–89; G3: 30–59 ml/min/1.73m^2^). In line with the National Kidney Foundation guidelines [25], albuminuria will be classified using two independent values of ACRs measured within a 3-month period, and a third if the classification differs between the first two samples. We define normo-, micro- and macro-albuminuria as an ACR of < 2.5, 2.5–25, > 25 mg/mmol for men, respectively, and as ACR < 3.5, 3.5–35, > 35 mg/mmol for women, respectively.

Participants are enrolled in the study following provision of written informed consent. Eligibility criteria can be checked via medical records or by performing additional assessments if no data available (e.g. eGFR). If no ACR measurement is available from the previous 3 months a random urine sample for ACR analysis will be collected following consent.

### Baseline study assessments

#### Participant preparation

Participants are required to be on stable diabetes and hypertension related treatment (though dose changes to current medications are allowed) for the 3 months prior to study assessments. Study assessments will be performed in the morning following an overnight fast (> 8 h). Medications may be withheld or altered on the day of the study visit to ensure participant wellbeing (e.g. omitting morning insulin injection to maintain blood glucose levels) and integrity of the study. The study visit will include a checklist to record the adherence to instructions (additional file 3.1). A point of care glucose measurement will be performed upon participant arrival and the visit will be cancelled if glucose levels are below 3.5 mmol/L or if the participant reports a symptomatic hypoglycaemic event on the morning of the visit. If the visit goes ahead, blood samples will be taken first. All other assessments are performed following a standardised meal of 2 slices brown bread, butter and a glass of water (250 mL).

#### MRI biomarkers

Fifty nine primary MRI biomarkers will be recorded (see additional file 1.1 for a full list), characterising general body composition (e.g. visceral fat volume, pancreatic and liver fat fraction), renal morphology (e.g. parenchymal volume, cortical thickness), renal tissue structure (e.g. MR relaxation times, apparent water diffusion coefficient), renal hemodynamics (e.g. cortical perfusion, renal artery blood flow), filtration (e.g. single-kidney GFR, filtration fraction). All MR scanning is performed at 3 T on Siemens, Philips and General Electric scanners. MRI data are uploaded on a central XNAT database hosted by SIB and quality controlled within 48 h by the central processing site.

The MRI protocol takes approximately 1 h and 10mins and involves the injection of a quarter dose of clinical macrocyclic MRI contrast agent. The protocol was first developed on the reference Siemens scanner in Leeds using an iterative optimisation guided by the NIST (National Institute of Standards and Technology) phantom and healthy volunteers. The resulting final protocol was then characterised on each MRI vendor using a repeatability study in healthy volunteers to determine within-site variability (5 volunteers with 4 scans each). The NIST phantom is scanned at regular intervals in all sites to check for between-site calibration. Full details of the MRI acquisition protocol on the 3 T Siemens reference scanner in Leeds can be found in additional file 1.2.

#### Renal ultrasound

Kidney size will be non-invasively determined from longitudinal and transversal images of each kidney. Resistive index (RI), indicator of the resistance to flow within the kidney, will be determined from three measurements in each kidney (upper, mid and lower poles). The mean of the three measurements will represent RI for each respective kidney. A list of US biomarkers is provided in the additional file 3.7 and the Standard Operating Procedures (SOPs) for US scanning are in additional file 1.3.

#### Blood and urine sampling

Fasting blood samples (~ 70 ml designated for iBEAt central requirement) will be collected from each participant for participant characterisation and biomarker analysis. Glycated haemoglobin (HbA1c), full blood count and fasting glucose assessments will be performed locally (additional file 3.4). The remaining plasma and serum samples will be processed and stored following a standardised protocol (see additional files 2.1-2.3). A first morning urine void and one additional morning void (same day) are collected by all participants. A small proportion of the first morning void is sent to the local laboratories for ACR assessment. The remainder of the first morning and second void are then processed and stored following a standardised protocol (see additional files 2.1-2.3).

The standardised sample collection and processing protocol, informed by PROVALID and NEPTUNE trials [26, 27], was developed to maximise the utility of stored samples for future biomarker analysis (e.g. lipidomics, RNA analysis, urinary vesicles and urinary sediment) within BEAt-DKD and to form a biobank for future DKD related studies. A separate check is performed to confirm that all samples are collected and processed according to protocol (additional file 3.8).

The central laboratory is located at the Clinical Research Centre (CRC) facility in Malmö (University of Lund). The central lab will prepare and distribute kits with sample collection and processing materials for each patient labelled and barcoded with their unique study ID. Each kit comprises of 66 storage tubes per patient. The samples will be temporarily stored at each recruiting site, with regular shipments returning them to the biobank in Malmö. Samples will be stored under secure conditions and monitored with a dedicated electronic sample tracking system (Laboratory Information Management Systems). A small volume of blood and urine will be analysed at the central laboratory in Malmö for known clinical biomarkers according to standardised methods, e.g. renal function (serum creatinine, cystatin C, potassium and albumin), lipid profile (total cholesterol and sub-fractions, triglycerides) and c-reactive protein. The remainder will be stored for future analyses by BEAt-DKD investigators. The samples will also remain available for secondary research provided approval is granted by the iBEAt steering committee.

#### Physical examination

The core physical examination assessments include blood pressures (sitting and standing blood pressures) and anthropometrics (height, weight, waist and hip circumference). See additional file 3.2 for details.

#### Medical history

A detailed medical history (including, for example, current medications, smoking history and presence of co-morbidities) is also collected. See additional files 3.3 and 3.6 for data fields that are captured.

#### Routine laboratory data

Routine local laboratory data will be captured from medical records to aid in the interpretation of the results by tracking temporal changes at a finer time scale than the yearly follow-ups. Only laboratory values available for clinical indication will be captured at this time. Additional file 3.5 lists the data fields to be captured but missing data from the local chart is not deemed a protocol violation.

### Follow-up study assessments

The blood and urine collection, medical history and physical examination will be repeated at 1, 2 and 3 years (± 3 months) following study enrolment. For participants who are unable to attend the local research centre for an annual follow-up visit but are still willing to participate in the study, an update on their medical history will be collected via direct communication with the participant and / or by accessing their available medical records.

### Data management

Clinical images, associated data and metadata will be stored using the XNAT platform (www.xnat.org) hosted on the dedicated BEAt-DKD server at SIB. Clinical study data will be managed using REDCap (www.project-redcap.org), also installed on the dedicated BEAt-DKD server. All variables will be recorded on iBEAt central case report form (CRFs – see additional files 3.0-3.8) and uploaded onto the central RedCap instance. It is envisaged that the iBEAt clinical study will be set up as a federated node enabling remote analysis of the data generated in the future, and integration of the iBEAt data with other datasets collected in BEAt-DKD.

### Statistical considerations

#### Sample size

There are insufficient a priori data available to perform a reliable formal power calculation for this study. Thus, a more pragmatic approach was adopted, with the sample size taking into account the feasibility aspects of the study, for example, the number of imaging facilities and the estimated rate of recruitment in each centre. This produced a target population of 500 patients, which will result in the largest quantitative imaging DKD study, to date, both in terms of patient numbers and regarding patient follow-up. Participants will be recruited across various stages of DKD, as measured by ACR (A1, A2, A3) and eGFR (G1 + G2, G3). This will produce a heterogeneous population enabling the evaluation of the associations between imaging biomarkers and DKD in T2D patients.

#### Statistical analysis plan

Descriptive statistics of all covariates across the study centres will assess the bivariate relationships between sets of related covariates. A cross-sectional analysis will be performed using data collected at baseline, as well as a longitudinal analysis using the imaging data collected at baseline and blood and urine markers collected annually. Given the large number of covariates in the study, a variable selection and regularisation method such as LASSO [28] or the elastic net regularisation [29] will be used. Modelling will use linear models for the cross-sectional analyses, and linear mixed effects models for the longitudinal analysis. The analyses will be performed separately in each ACR / eGFR stratum, and the modelling of the whole cohort will account, whenever possible, for differences in potential associations across the strata. We will adjust for multiple comparisons as needed. If any renal imaging biomarkers are identified as promising early markers of DKD progression, they will be used in risk prediction. Their predictive accuracy as measured by prediction error, receiver operating characteristics curve (ROC) and the area under the ROC (area under the curve, AUC) will be evaluated using cross-validation. A conservative approach will be adopted in all analyses, for example, limiting the number of models fitted and statistical tests performed. All analyses will be treated as exploratory and hypotheses generating, rather than hypothesis testing.

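### Imaging biomarkers are identified first and cross-validated second, apparently in the same participants; unless selection is repeated inside the folds, the reported AUC is likely to be optimistic

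*Protocol article*

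**What the plan says.** The Statistical analysis plan section of the protocol article describes three steps.

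- **Selection.** Because there are many covariates, "a variable selection and regularisation method such as LASSO [28] or the elastic net regularisation [29] will be used". The data used are described as follows: "The analyses will be performed separately in each ACR / eGFR stratum, and the modelling of the whole cohort will account, whenever possible", for differences between strata.
- **Carrying forward.** "If any renal imaging biomarkers are identified as promising early markers of DKD progression, they will be used in risk prediction".
- **Scoring.** For the biomarkers so identified, prediction error, the ROC curve and "the area under the ROC (area under the curve, AUC) will be evaluated using cross-validation".

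The candidate pool is large. The MRI biomarkers section states "Fifty nine primary MRI biomarkers will be recorded", and ultrasound, clinical and fluid measures come on top. The Sample size section says "There are insufficient a priori data available to perform a reliable formal power calculation for this study" and sets the target of 500 on feasibility.

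The same statistical section promises adjustment for multiple comparisons where needed and a conservative approach, and it labels all analyses exploratory.

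**The concern.** What is cross-validated, as the text reads, is the chosen set of biomarkers and not the process that chose it. If the choice used everyone's follow-up, each held-out participant has already influenced which predictors are in the model. Cross-validation then removes the overfitting of the coefficients and leaves in the overfitting of the selection.

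No separate data set is assigned to repair this. The training and test split in Ancillary study 3 concerns image processing. The Data management section foresees integration with other consortium data sets but does not assign them to validating a risk model.

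At stake is the AUC and prediction error attached to any imaging biomarker put forward as prognostic. These are the only measures of predictive accuracy that the section names, and they could help decide which biomarkers are pursued. An inflated value would make a weak or null biomarker look usable.

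**Working it through.** The article states no AUC, prediction error or power figure, so there is nothing to reproduce. The size of the effect was simulated.

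**From the article:** 59 candidate MRI biomarkers; 500 participants; six ACR by eGFR cells (A1, A2, A3 by G1+G2, G3), so 500 / 6 ≈ 83 per cell if equal.

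**Assumed:** 20% of participants progress (100 of 500); common correlation among biomarkers 0 to 0.6; either no true biomarker or three, each with a log-odds of 0.2 or 0.4 per SD; 10-fold cross-validation; LASSO with a fixed penalty, or the five biomarkers most correlated with outcome; equal strata.

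**Room for false leads.** At an unadjusted 0.05 level, 59 × 0.05 = 2.95 false leads are expected. If the biomarkers are independent, the chance of at least one is 1 − 0.95^59 = 0.95.

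**Optimism** = cross-validated AUC with selection made once on all participants, minus the AUC of that model in new participants. For n = 500, 20% progression, correlation 0.3, selection on the binary outcome:

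| Selector | True signal | Selection outside folds | Selection inside folds | New participants | Optimism |
|---|---|---|---|---|---|
| LASSO | none | 0.599 | 0.530 | 0.502 | +0.097 |
| LASSO | 0.2 | 0.632 | 0.582 | 0.580 | +0.052 |
| LASSO | 0.4 | 0.716 | 0.693 | 0.690 | +0.026 |
| Top 5 | none | 0.593 | 0.507 | 0.500 | +0.093 |
| Top 5 | 0.2 | 0.623 | 0.583 | 0.586 | +0.037 |
| Top 5 | 0.4 | 0.711 | 0.684 | 0.687 | +0.024 |

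The LASSO rows average only over replicates in which something was selected (44 of 60 with no signal), which suits a plan that proceeds only if a biomarker is found.

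**Correlation.** With no signal, moving it from 0 to 0.6 gives +0.08 to +0.10 for LASSO and +0.05 to +0.12 for the top five. With log-odds 0.4 and correlation 0.6, LASSO optimism is only +0.005.

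**Selecting on the slope.** The plan models eGFR slope, so a closer version picks the top five by correlation with the continuous slope and scores the AUC for the worst 20% of slopes. With no signal, n = 500 and correlation 0.3, two runs gave a mean AUC of 0.54 and 0.55 against a true 0.50, that is +0.04 to +0.05; in the second the 5th to 95th percentile range was 0.47 to 0.61. With weak or moderate signal the excess was about +0.01. A rerun that changed only the selection target gave 0.55 for slope and 0.59 for the binary outcome, so this choice explains most of the gap from the table.

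**Strata.** At n = 83 (about 83 × 0.20 ≈ 17 progressors) with no signal, the AUC was 0.58 and 0.62 in two slope-selected runs and 0.66 to 0.73 when selection used the binary outcome.

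**Effect of the fix.** With selection repeated inside the folds, the AUC was within about 0.03 of its value in new participants in every n = 500 scenario, and within about 0.04 at n = 83.

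**Exception.** Univariate screening at p < 0.05, a selector that the article does not name, gave −0.06 to 0.00 when correlated biomarkers carried true signal. It kept about 20 to 59 of them in an unpenalised model.

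**The case against.** The strongest objection is that this is a condensed article with one paragraph of statistics. Whether selection sits inside the folds is a detail that a full analysis plan would normally settle. LASSO and elastic net can both be nested, and nothing in the text rules that out. That part stands: a reader might infer that the article commits to selecting on the full cohort outside the folds, and it does not say so. But the article is not merely silent. It states an order, and followed literally that order leaks information from the held-out participants.

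A second objection is that the step may rarely be reached on noise. It is conditional on a biomarker being found. In a simulation with no signal (n = 500, correlation 0.3, 100 replicates), a Bonferroni or Benjamini-Hochberg gate passed any biomarker in 6% of replicates, LASSO at the one-standard-error penalty in 0%, and LASSO at the minimum-error penalty in 37%. This stands as a limit on how often pure noise would be scored. It does not remove the bias once a biomarker has passed.

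A third objection is that the AUC is not the study's main evidence. A reader might take it to be so, but the stated objectives are association with DKD severity (primary) and with eGFR slope (secondary); risk prediction is a follow-on. That stands and lowers the severity. The exploratory label does too, although it does not change how the AUC is computed.

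**Conclusion.** The point holds in a qualified form. As written, identification precedes cross-validation, apparently in the same participants and with no independent cohort named. Unless selection is repeated inside the folds, the reported AUC is likely to be optimistic. Under the assumed settings, and at correlation 0.3, the excess is roughly +0.04 to +0.10 at n = 500 when there is no true signal. It shrinks towards zero with stronger signal and is larger in small strata.

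Two stronger readings are not supported. The first is that the AUC will certainly be too high: the bias was +0.005 in one LASSO setting and zero to negative under one selector that the article does not name. The second is that inflated AUCs will be reported for each stratum: the article does not clearly say that risk prediction is run by stratum, and 83 per stratum assumes equal cells.

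All magnitudes rest on assumed event rates, correlations and effects. Prediction error was not simulated; the same mechanism is expected to apply to it. Severity is moderate.

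**What to change.** Add a sentence to the statistical analysis plan: biomarker selection, penalty tuning and model fitting are all repeated within each training fold (nested cross-validation), and the resulting AUC and prediction error are reported as the predictive accuracy. A bootstrap optimism correction that repeats the same whole pipeline in each resample would serve equally well. If nesting was always intended, the sentence simply removes the literal reading.

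The cost is more computing and, probably, a slightly lower reported AUC. No visits, samples or participants are added. Leave-one-centre-out validation would also show transfer across the three scanner vendors, but it is optional and not needed to cure this problem.
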